##### Behavioral assessments

At pre- (1st session), mid- (7th session), end- (13rd session), and follow-up sessions (2 and 6 weeks after the end of the intervention), participants will be asked to answer the following behavioral task. It will consist of one block of stimulus pairs containing 244 pairs that will be presented at 60 dB via the Shure SRH1840 audio headset. The stimulus pair will be composed of either identical stimuli (50%; two neutral stimuli), or different stimuli [one neutral and one of the emotional deviants (50%; anger (10%), disgust (10%), fear (10%), happiness (10%), or sadness (10%)]. Fifty percent of pairs that contain a deviant stimulus will be composed of 1 neutral followed by 1 emotional stimulus, and 50% will be composed of 1 emotional followed by 1 neutral stimulus. Word pairs will be equally uttered with a male, woman, or child voice. The within-pair stimulus onset asynchrony will be 1,300 ms, and the between-pair stimulus onset asynchrony will be 2,600 ms. The order of stimulus pairs will be randomized between participants, but the stimulus sequence will be fixed. During this approximately 20-min task, participants will have to answer by pressing previously instructed keys on a laptop keyboard, if the emotional prosody of both stimuli of each pair will be the same or different. If they choose different, they will have to mention the emotion conveyed by the deviant (anger, disgust, fear, happiness, or sadness). Reaction times and correct/incorrect answers will be recorded. To make sure that the participant understands the task, three training trials will be presented before the test. Autistic participants will be accompanied by their parent if necessary.

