##### Statistical analysis on behavioral data

Group comparisons of reaction times will be conducted by a Group × Stimulus (neutral, anger, disgust, fear, happiness, or sadness) repeated measures ANOVAs on each assessment session separately. Time comparisons will be conducted by Assessment Session × Stimulus on each group separately. Normality of reaction times will be assessed by Shapiro–Wilk test. In case of non-parametric distribution of the data, a transformation will be applied. Mauchly’s test of sphericity will be used to evaluate homogeneity of variances and co-variances. In case of violation of sphericity, a Greenhouse-Geisser correction will be applied in order to test main effects significance. Post-hoc comparisons will be conducted to assess specific differences (Tukey procedure).

Group comparisons of number of correct answers will be conducted by one-way ANOVAs for each deviant and assessment session separately. Time comparisons (between assessment sessions) will be tested by one-way ANOVAs on number of correct answers for each deviant and each group separately. Normality and homogeneity of variances will be assessed by Shapiro–Wilk and Bartlett tests, respectively. In case of non-parametric distribution of the data, Kruskal–Wallis test will be applied. *Post hoc* comparisons will be conducted to assess specific differences (Tukey after ANOVA, Wilcoxon tests with *p*-value adjustment by Holm method after Kruskal–Wallis).

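### Accuracy is analysed only on emotional pairs, so the score cannot separate better prosody discrimination from a greater readiness to answer 'different'

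*Protocol article*

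**What the plan says.** The task is set out in the protocol article under Behavioral assessments (Stage 3). On its size: "It will consist of one block of stimulus pairs containing 244 pairs". On its composition: "The stimulus pair will be composed of either identical stimuli (50%; two neutral stimuli), or different stimuli". A different pair holds one neutral word and one emotional deviant, and each of the five emotions makes up 10% of all pairs. The response has two steps: same or different first, and then "If they choose different, they will have to mention the emotion conveyed by the deviant". On what is kept: "Reaction times and correct/incorrect answers will be recorded".

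Under Statistical analysis on behavioral data, the group analysis of accuracy is: "Group comparisons of number of correct answers will be conducted by one-way ANOVAs for each deviant and assessment session separately". The time analysis uses "one-way ANOVAs on number of correct answers for each deviant and each group separately". In the same section, the reaction-time analysis lists neutral as a stimulus level beside the five emotions; the accuracy analysis does not. The Discussion treats more correct answers at the end and follow-up assessments as higher accuracy in discriminating emotions.

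**The concern.** 'Deviant' in this task means an emotional pair, so the accuracy outcome is a count of hits. A hit count depends on two things: how well the child tells emotional from neutral prosody, and how ready the child is to answer 'different'. Only answers to the identical pairs can pull these apart, and no stated accuracy analysis uses them. Naming has the same weakness, because a child who favours one label collects hits on that emotion.

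Groups 1 and 2 have 12 sessions in which they are asked which emotion is conveyed and are praised for correct answers. Group 3 has none. All groups meet the same task at five assessments. Either kind of exposure could change response habits, and the planned score would record such a change as a change in discrimination. The article also does not say whether 'correct' on an emotional pair needs the right emotion name or only the answer 'different'. The size of the problem depends on this.

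**Working it through.** **Inputs from the article.** There are 244 pairs. Identical pairs: 0.50 × 244 = 122. Pairs per emotion: 0.10 × 244 = 24.4 (nominal, since 244 does not divide evenly). There are five labels, so a guessed name is right with probability 0.2. The planning effect for number of correct answers is d = 0.8.

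**The plan's own figure.** The article states power 0.92 for this outcome with 18 per group. A one-way ANOVA with four groups of 18 and f = d/2 = 0.4 (my conversion, not stated) gives 0.80, so the figure is not reproduced on that reading. That is a separate matter. Nothing below uses the sample size, and d = 0.8 serves only as a yardstick.

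**Check 1: a child with no discrimination.** Let the probability of answering 'different' rise from 0.3 to 0.9 on every pair.

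| Quantity | At 0.3 | At 0.9 |
|---|---|---|
| Correct per emotion, detection only (24.4 × p) | 7.3 | 22.0 |
| Correct per emotion, name also guessed right (24.4 × p × 0.2) | 1.5 | 4.4 |
| Correct identical pairs (122 × (1 − p)) | 85.4 | 12.2 |
| Same/different accuracy, all pairs | 0.50 | 0.50 |

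The planned analysis sees only the first or second row, and both rise.

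**Check 2: fixed, non-zero discrimination.** I use an equal-variance signal-detection model with hit rate H = Φ(d'/2 − c) and false-alarm rate FA = Φ(−d'/2 − c). Assumed: d' = 1, with c moving from 0.5 to 0.

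- H: Φ(0) = 0.500 to Φ(0.5) = 0.691, a rise of 19.1 points, or 12.2 to 16.9 of 24.4 pairs.
- FA: Φ(−1) = 0.159 to Φ(−0.5) = 0.309, so correct identical pairs fall from 102.6 to 84.4 of 122.
- d' is unchanged at 1. H − FA moves from 0.341 to 0.383 (about 4 points), so it is nearly but not exactly free of the shift.

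**Size under each meaning of 'correct'.** The rise is divided by an assumed between-child SD of 20 points, with 15 and 25 as the range. The same SD is kept for all rows, which is a further assumption.

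| Scoring | Rise (points) | d at SD 20 | d at SD 15 | d at SD 25 |
|---|---|---|---|---|
| Detection only | 19.1 | 0.96 | 1.3 | 0.77 |
| Naming required, 80% named correctly | 15.3 | 0.77 | 1.0 | 0.61 |
| Naming required, 50% named correctly | 9.6 | 0.48 | 0.64 | 0.38 |
| Naming required, added 'different' answers named by chance | 3.8 | 0.19 | 0.25 | 0.15 |

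The rise is positive in every row. On an emotional pair 'same' can never be correct, while 'different' has some chance of being followed by the right name.

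**The case against.** Four points on the other side have weight.

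- **Naming limits the effect.** If 'correct' requires the right emotion, a child cannot gain much merely by answering 'different' more often; a pure guesser gains one fifth as much. A reader might infer that a criterion shift alone exceeds the planned effect of 0.8. That does not follow. It needs detection-only scoring or a small SD, and at SD 25 even detection-only scoring gives 0.77.
- **The shift is not documented.** A reader might infer that the score is biased in favour of the intervention. The training asks which emotion a prosody conveys and corrects wrong answers; it does not reward answering 'different'. Neutral speech is used in the sessions, and neutral appears to be among the six prosodies given a specific story. Training could make children stricter as easily as more liberal.
- **The Group 1 versus Group 2 contrast is little affected.** Both groups get the same question-and-answer practice and differ only in the voices used. A practice-driven shift should largely cancel in the contrast that evaluates the synthesized voices.
- **Other outcomes do not share the problem.** The passive EEG task needs no overt response, and the ASRS is rated by parents. The article names no primary outcome, so accuracy cannot be called the main one.

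All four stand and limit the point. A fifth, that scoring detail may sit in a fuller document, carries less weight. The article itself states the score, the strata and the test, and it includes neutral for reaction times but not for accuracy.

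**Conclusion.** The concern holds as a limitation of the stated score. The number of correct answers per deviant cannot tell better discrimination from a changed readiness to answer 'different', and no stated accuracy analysis would reveal the difference. It matters mainly for Groups 1 and 2 against Group 3 and for the within-group session comparisons. Under the assumed d', criterion shift and SD, an apparent effect of about 0.96 could arise with detection-only scoring (1.3 to 0.77 over SD 15 to 25), and about 0.2 to 0.8 at SD 20 if naming is required, with discrimination unchanged. These figures show what the score could hide. They are not an estimate of a bias that will occur, and the documents fix neither its size nor its direction.

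**What to change.** In Statistical analysis on behavioral data:

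1. State whether 'correct' on an emotional pair means detection, or detection plus the correct emotion name.
2. Analyse same/different discrimination per child, session and emotion with d', taking hits from that emotion's pairs and false alarms from the identical pairs, with a log-linear correction (add 0.5 to each count and 1 to each number of pairs). Hit rate minus false-alarm rate is a simpler alternative, less fully protected against a criterion shift.
3. For naming, use an unbiased hit rate: correct uses of a label squared, divided by the product of that emotion's pairs and all uses of the label.
4. Keep the raw counts as descriptive results.

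The cost is small. The child already gives every response needed, so no trials, visits or participants are added. The same/different answer and the chosen label must be stored separately, not only as correct or incorrect. The power stated for number of correct answers under Participants, Intervention (18 per group for group comparisons, 15 for session comparisons) must be rechecked, because d' from about 24 pairs per emotion has a different variance from a raw count.

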##### ERPs

For ERP amplitude analysis, electrodes will be grouped according to ROIs described in section “Data Analysis.” Maximum peak time windows used for data analysis of ERPs will be identical to the one mentioned in section “Data Analysis.” MMN, P200, P3a, LPP will be under study.

Event-Related Potentials will be extracted by averaging the data obtained for standard and deviant stimuli, and for each condition independently. The ERPs elicited by standard stimuli will be subtracted from the ERPs elicited by deviants to calculate difference waves. The mean ERP amplitude will be calculated as follows. For standard stimuli, group and assessment session average peak latencies will be determined from all ROIs for TD and ASD separately. Mean amplitudes will be determined by considering a ±50-ms time window centered to the grand mean peak latency. For deviant stimuli, mean amplitudes will be calculated from the difference waves at ROIs. Mean amplitudes will be determined by considering a ±50-ms time window centered to the grand mean peak latency (Kujala et al., 2007; Paris et al., 2018).

##### Statistical analysis on ERPs data

The statistical significance of ERP components will be tested by comparing their mean amplitudes to zero at ROIs using one-sample *t*-tests. This method will allow us to focus exclusively on significant responses, and to distinguish significant scalp distributions from noise. Statistically significant ERPs will be considered for further amplitude analysis.

Group comparisons will be conducted by Group × ROI repeated measures ANOVAs on each ERP and assessment session separately, for standard stimuli. Similarly, for deviant stimuli, Group × ROI × Deviant repeated measures ANOVAs will be performed.

For standard stimuli, time comparisons will be conducted by Assessment Session × ROI repeated measures ANOVAs on each ERP and group separately. For deviant stimuli, Assessment Session × ROI × Deviant repeated measures ANOVAs will be performed.

Scalp distribution comparisons for standard stimuli will be assessed by Group × Laterality (FP1, F3, F7, T7, C3, P3, P7, O1/AFz, Fz, CPz, Cz, POz, Pz/FP2, F4, F8, T8, C4, P4, P8, O2) repeated measures ANOVAs on each ERP and assessment session separately. For deviant stimuli, Group × Laterality × Deviant repeated measures ANOVAs will be conducted.

For all amplitude analysis, normality will be assessed by Shapiro–Wilk test. In case of non-parametric distribution of the data, a transformation will be applied. Mauchly’s test of sphericity will be used to evaluate homogeneity of variances and co-variances. In case of violation of sphericity, a Greenhouse-Geisser correction will be applied in order to test main effects significance. *Post hoc* comparisons will be conducted to assess specific differences (Tukey procedure).

All statistical analysis will be performed with R software. Level of significance will be set at *p* < 0.05.

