#### Data Analysis

##### Statistical analysis on ASRS scores

Group comparisons will be conducted by one-way ANOVAs on T-scores for each assessment session and symptom domain (Social/Communication, DSM-IV-TR, Peer and Adult Socialization, and Social/Emotional Reciprocity) separately.

Time comparisons (between assessment sessions) will be tested by one-way ANOVAs on T-scores for each group and symptom domain (Social/Communication, DSM-IV-TR, Peer and Adult Socialization and Social/Emotional Reciprocity) separately.

Normality and homogeneity of variances will be assessed by Shapiro-Wilk and Bartlett tests, respectively. In case of non-parametric distribution of the data, Kruskal-Wallis test will be applied. Post-hoc comparisons will be conducted to assess specific differences (Tukey procedure in case of ANOVA, Wilcoxon tests with *p*-value adjustment by Holm method in case of Kruskal–Wallis test).

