##### Intervention

Autistic and TD participants involved in this study will have to meet the same criteria than those described in Stage 2. However, participants from Stage 2 will not be included in Stage 3 in order to avoid any bias elicited by a former exposition to the synthetic voices under study.

Sample size estimation was calculated with G^∗^Power software version 3.1.9.7 (Faul et al., 2007) for Cohen’s d effect size index of 0.8, correlations among repeated measures of 0.5, and statistical significance set at *p* < 0.05. For ERP analysis, results indicated that 13 participants in each group would be enough to provide an estimated power of 0.92 for group comparisons, and 11 participants in each group would be enough to provide an estimated power of 0.91 for assessment sessions comparisons. For behavioral analysis on reaction times, results indicated that 13 participants in each group would be enough to provide an estimated power of 0.91 and seven participants in each group would be enough to provide an estimated power of 0.93 for assessment sessions comparisons. For behavioral analysis on number of correct/incorrect answers, results indicated that 18 participants in each group would be enough to provide an estimated power of 0.92 for group comparisons, and 15 participants in each group would be enough to provide an estimated power of 0.90 for assessment sessions comparisons (Cohen’s d effect size index of 0.8, statistical significance set at *p* < 0.05). For behavioral analysis on ASRS scores, results indicated that 16 participants in each group would be enough to provide an estimated power of 0.92 and 18 participants in each group would be enough to provide an estimated power of 0.90 for assessment sessions comparisons.

A total of 72 participants will take part to this Stage and will be divided in four groups:

•Group 1: autistic children receiving robot, synthesized and human voices intervention (18 participants).•Group 2: autistic children receiving robot and human voice intervention (18 participants).•Group 3: autistic children without receiving intervention (18 participants).•Group 4: TD children without receiving intervention (18 participants).

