This project of investigation might encounter some pitfalls and unexpected results. Non-professionalism of actors recruited for emotional recordings during Stage 1 may affect the reliability of required prosodies. Nevertheless, the number of volunteers will be increased in order to generate four times more utterances than necessary to enable the selection of best actor participants. Furthermore, emotion recognition accuracy will be validated by supervised learning algorithm to ensure the quality of emotion discrimination based on acoustic features. Stage 2 aims to explore emotional recognition impairments in autism triggered by naturalness of human voices. We expect to observe a diminution of the amplitude of ERPs in the autistic population as a reflect of decreased attentional, sensorial, and cognitive emotional processing (Lartseva et al., 2015; Lindström et al., 2016, 2018). The autistic condition may also be characterized by hemispheric lateralization anomalies due to lateralized compensatory brain activity (Subbaraju et al., 2018). Impairments are expected to fade with the decreasing naturalness of voice stimuli. However, in the opposite case, no effect of naturalness on neural emotional processing by autistic children would be an evidence that the modulated acoustic parameters would not participate to autistic impairments. In the latter situation, or in case of enhancement of autistic impairments triggered by naturalness modulations, the acoustic edition of the stimuli will be reconsidered. Finally, Stage 3 expects the implementation of less natural voices in a robot-based intervention with the aim of improving emotion detection by autistic children. The 2-week intervention may imply a high rate of withdrawals whereas the sample size needed is relatively high. However, upon completion, we expect the intervention to trigger a reduction of autistic impairments (reduction of symptomatology, higher EEG activity, higher behavioral accuracy for emotion discrimination: smaller reaction times, and higher correct answers at end- and follow-up assessments).

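### The Stage 3 session comparisons of ERPs and reaction times drop any child with one missing session, although the plan itself warns of possibly high withdrawal

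*Protocol article*

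**What the plan says.** The protocol article fixes the session analyses by outcome.

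- **ERP amplitudes** (Stage 3, Statistical analysis on ERPs data): for standard stimuli, "time comparisons will be conducted by Assessment Session × ROI repeated measures ANOVAs on each ERP and group separately". The next sentence covers deviants: "For deviant stimuli, Assessment Session × ROI × Deviant repeated measures ANOVAs will be performed". Mauchly's test and the Greenhouse-Geisser correction follow.
- **Reaction times** (Statistical analysis on behavioral data): "Time comparisons will be conducted by Assessment Session × Stimulus on each group separately", with the same sphericity procedure, so this too is a repeated-measures ANOVA.
- **Correct answers** (same section): "Time comparisons (between assessment sessions) will be tested by one-way ANOVAs on number of correct answers for each deviant and each group separately".
- **ASRS** (Statistical analysis on ASRS scores): "Time comparisons (between assessment sessions) will be tested by one-way ANOVAs on T-scores for each group and symptom domain".

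EEG and behavioral data are collected five times: pre, mid, end, and 2 and 6 weeks after the intervention. The ASRS is collected three times. Group comparisons of all outcomes are made at each session separately.

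On withdrawal, the Discussion says: "The 2-week intervention may imply a high rate of withdrawals whereas the sample size needed is relatively high". It gives no rate. Stage 3 enrols 18 children in each of four groups, which equals the largest requirement listed under Participants, Intervention; for correct answers, "results indicated that 18 participants in each group would be enough to provide an estimated power of 0.92 for group comparisons".

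**The concern.** The plan names a possible withdrawal problem and also fixes, for two of its outcomes, an analysis that handles withdrawal poorly. A child who attends four of five assessments contributes nothing to the ERP or reaction-time session comparison. For ERPs, one recording lost to artifact has the same effect. At stake are data already collected from children who are hard to recruit, the precision of the comparisons meant to show change over time, and a result that describes only children with a full record. The point does not depend on missing-data detail that an article may leave to a full analysis plan, because the named method itself requires complete records.

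**Working it through.** **Inputs from the protocol article.** Cohen's d = 0.8, correlation among repeated measures 0.5, significance level 0.05, five assessments, 18 enrolled per group, and 11 per group for power 0.91 in the ERP session comparison.

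**Assumptions.** f = d/2 = 0.4. Withdrawal rates are assumed because none is given. Loss is taken to start after the pre-assessment, since withdrawal caused by the intervention cannot precede it, and to be permanent.

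**Step 1: reproduce the plan's figure.** For one group with n children and m = 5 sessions, the F test has noncentrality f² × n × m / (1 − 0.5), with 4 and 4(n − 1) degrees of freedom. At n = 11 the noncentrality is 0.16 × 11 × 5 / 0.5 = 17.6 and power is 0.905, against the stated 0.91. The figure reproduces.

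**Step 2: power with fewer complete children.** The same formula gives 0.993 at 18, 0.968 at 14, 0.933 at 12, 0.905 at 11, 0.867 at 10 and 0.818 at 9.

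**Step 3: complete children under assumed loss.** Let q be the loss at each of the four later assessments and s = 1 − q. Complete children number 18 × s⁴. The share of planned observations recorded is (1 + s + s² + s³ + s⁴)/5. The share of recorded observations that listwise deletion discards is 1 − s⁴ divided by that quantity.

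| q | Complete of 18 | Planned observations recorded | Recorded observations discarded |
|---|---|---|---|
| 5% | 14.7 | 90% | 10% |
| 10% | 11.8 | 82% | 20% |
| 15% | 9.4 | 74% | 30% |

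**Step 4: thresholds.** Complete children fall below 11 of 18 when q exceeds 1 − (11/18)^(1/4) = 11.6%. They fall below half of a group when q exceeds 1 − 0.5^(1/4) = 15.9%. Sessions missed by children who later return, and unusable recordings, would add to the loss.

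**Step 5: slack in the other requirements.** The article lists eight per-group sizes:

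- ERPs: 13 (groups) and 11 (sessions)
- Reaction times: 13 and 7
- Correct answers: 18 and 15
- ASRS: 16 and 18

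Six of the eight are below 18. The two equal to 18 are correct answers between groups and ASRS between sessions. Both are one-way ANOVAs, so neither loses children listwise, but neither has room for any withdrawal. I give no reduced power for these two: at f = 0.4 their stated powers do not reproduce even at 18 (0.80 against 0.92, and 0.73 against 0.90), which is a separate matter.

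**The case against.** The strongest reply is that the session comparisons criticised here have the most room. ERP sessions need 11 of 18 and reaction-time sessions 7 of 18, so at 10% loss per later assessment both stated requirements are still met. That stands, and it limits the harm to power. It does not answer the discarding of about a fifth of the recorded observations in that case.

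A second reply is that an article may leave missing-data handling to a document not shown. That is true of analysis populations and of follow-up after stopping, and nothing is claimed about those. A later plan could avoid the listwise loss only by departing from the method named here.

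A reader might also infer more than the text supports:

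- **That most of the data will be lost.** The article says only that withdrawal may be high, and losing more than half of a group needs about 16% loss at each later assessment.
- **That the plan defines a completers' analysis.** The sentence "However, upon completion, we expect the intervention to trigger a reduction of autistic impairments" is an expectation about results in the Discussion and sets no analysis population.
- **That listwise deletion inflates the effect against the untreated autistic group.** The session ANOVAs are within group, and comparisons between groups are made session by session with the children present. Selective withdrawal could distort those comparisons, but its direction and size would rest on assumptions found nowhere in the article.
- **That every stated power fails once anyone withdraws.** Six of the eight requirements are below 18.

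**Conclusion.** The point holds for the ERP and reaction-time session comparisons. They are complete-case by the method named, over five assessments, in a stage where the plan itself foresees possible withdrawal. With 5% to 15% loss at each later assessment, about 14.7 down to 9.4 of 18 children per group would be analysed, and 10% to 30% of the recorded observations would be thrown away. ERP session power would fall from 0.993 at 18 to about 0.82 at 9, passing below the plan's own requirement of 11 when loss exceeds about 11.6% per assessment. These sizes depend on assumed rates and on permanent loss that starts after the pre-assessment. The lack of any withdrawal allowance matters separately for the two comparisons that need all 18. The plan should be changed, but the documents do not show that its conclusions would be invalid.

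**What to change.** In Statistical analysis on ERPs data and Statistical analysis on behavioral data, replace the repeated-measures ANOVAs over sessions with linear mixed models. Use session as a factor, ROI and Deviant (ERPs) or Stimulus (reaction times) as within-child factors, and a random child effect. A child-by-session term is advisable so that several values from one recording are not treated as independent. Fit the models to every available session of every child, in the group assigned.

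Under Participants, Intervention, state the expected retention and the power at the number expected to be retained, in particular for correct answers between groups and ASRS between sessions. Enrolment can stay at 18 per group.

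The cost is a change of wording and some extra model fitting in R, which the plan already uses. The results would rest on a missing-at-random assumption, which should be stated, and the quoted power would be slightly lower.
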